#### **11.4.4 Interim analyses**

The DSMB will meet for a single interim safety analysis on the first 100 patients randomized once the end of the time window for their 24 weeks study visit is reached. The Sponsor-Investigator and all Study investigators will receive the related DSMB advice blinded to study arm. In addition to the scheduled meetings, extraordinary meetings may be requested by DSMB members, the Sponsor-Investigator, or the Study Scientific Committee at any time. The DSMB will review the safety data and may make recommendations about the conduct of the trial (study interruption) should any safety concerns be identified. The interim analysis will be prepared by an independent, unblinded statistician.

#### **11.4.5 Safety analysis**

The proportion of serious adverse events across the different study time-points will be compared between the two treatment arms by mixed logistic regression model with a random effect on the subject after adjustment for the monitoring strategy.

The proportion of drug-related events across the different study time-points will be compared between the two treatment arms by mixed logistic regression model with a random effect on the subject after adjustment for the monitoring strategy.

The proportion of patients experiencing loss of future drug options defined as new intermediate or high-level resistance to one or more drugs to which the patient's virus was considered sensitive at trial entry will be compared between the two treatment arms by a multiple logistic regression model adjusted for the monitoring strategy.

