### 5.2 Secondary Outcomes

1. Proportion of patients maintaining HIV suppression defined as HIV-RNA <50 copies/ml throughout 48 weeks (+/- 21 days). A single blip defined as HIV-RNA <200 copies/ml during the study period is allowed as long as this value is followed by HIV-RNA <50 copies/ml;
2. Proportion of patients with HIV-RNA < 50 cp/ml at week 48 by FDA snapshot analysis; Proportion of patients experiencing loss of future drug options defined as new intermediate or high-level resistance to one or more drugs to which the patient's virus was considered sensitive at trial entry;
3. Time to loss of virological response (TLOVR) up to week 48 defined as the first of the two-confirmed HIV-RNA >100 copies/ml (at least two weeks apart);
4. Change in CD4 cell count from baseline to week 48 +/- 21 days;
5. Change in HIV-DNA level from baseline to week 48 +/- 21 days;
6. Change in lipidic profile (total cholesterol, high density lipoprotein-cholesterol, triglycerides, and low density lipoprotein-cholesterol) from baseline to week 48 +/- 21 days;
7. Change in glucose profile from baseline to week 48;
8. Change in Framingham-calculated cardiovascular risk from baseline to week 48;
9. Change in glomerular function rate from baseline to week 48;
10. Proportion of patients with an adverse event throughout week 48;
11. Proportion of patients with a serious adverse event (SAE) throughout week 48;
12. Proportion of patients with a CNS adverse event throughout week 48;
13. Proportion of patients new to DTG with CNS symptoms at 2 and 6 weeks after starting DTG;
14. Change in patients' health-related quality of life from baseline to weeks 12 and 48;
15. Assessment of patient's monitoring satisfaction from baseline to weeks 24 and 48 for patients in the patient-centered monitoring arm;
16. Assessment of the global satisfaction of the monitoring at week 48 for all patients (regardless of the randomisation arm);
17. Proportion of patients in the patient-centered monitoring arm expressing willingness to change monitoring options throughout 48 weeks;
18. Assessment of patient's treatment satisfaction at week 48;
19. Assessment of ARV treatment in the post study;
20. Study satisfaction at week 48;
21. Cost-effectiveness of study arms at 48 weeks;
22. Changes in patient weight from baseline to week 48.

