### 11.2 Determination of Sample Size

The first sample size calculation was based on the primary outcome for the comparison between DTG + FTC dual therapy and standard cART, i.e. the comparison between the proportions of patients in the two arms maintaining virologic suppression, using a two-sample proportion test (96). The following assumptions were made:

- Power 80%
- Significance level 0.025 (one-sided Z test of non-inferiority)
- 97% of patients with conventional cART will be virologically suppressed at week 48 (<100 copies/ml)
- 94% of patients on DTG + FTC dual therapy will be virologically suppressed at week 48 (<100 copies/ml)
- Non-inferiority margin of 12% (as in previous non-inferiority trials)(97-104). We chose 12% noninferiority margin because there is no difference in terms of resistance acquisition between 10% and 22% virological failure.

Sample size of 83 patients in each group (total sample size, 166 patients) to achieve 80% power to detect a non-inferiority margin difference between the group proportions of -0.12 was calculated. The power was computed for the case when the actual cART group proportion is 97% and the actual DTG + FTC dual therapy group proportion is 94%. To allow for at least 10% loss to follow-up and also for the randomisation in two steps in this 1:1:1:1 trial, we will aim to recruit **a total of 184 patients**.

The second sample size calculation was based on the primary outcome for the comparison between simplified monitoring and standard monitoring, i.e. the comparison between mean direct costs in the two arms (105). The following assumptions were made:

- Significance level 0.05 (two-sided t-test)
- Direct costs are CHF 25,000 per year (standard deviation (SD) CHF 8,000) with conventional monitoring
- SDs are equal in the two groups (CHF 8,000)

With sample sizes of 92 patients in each group, we will have approximately 55% power to detect a 10% difference in costs, and 99% power to detect a 25% difference in costs. We will also have substantial power to detect small-to-moderate differences in many of the secondary outcomes, e.g. changes in CD4 cell counts or health-related quality of life. The exceptions are rare outcomes such as adverse events, resistance or clinical complications for which the statistical power to detect differences will be low.

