#### 11.4.2 Primary analysis

As a first step in this factorial trial, we will test for an interaction between the type of drug treatment and the monitoring type in order to assess if treatment effect is different depending on the type of monitoring. If the test is non-significant we will combine the two types of monitoring for the drug therapy comparison and the two drug therapies for the monitoring comparison. Otherwise, the trial will be analysed as a four-arm trial with a hierarchical testing approach.

For the primary comparison of the primary outcome between the two treatment arms, we will obtain the proportion of patients with viral suppression for 48 weeks in each arm, and compute a Mantel-Haenszel risk difference (DTG+FTC - cART) stratified for the monitoring type with a two-sided 95% confidence interval (107). If the lower confidence limit is higher than -12% we will conclude non-inferiority. If the lower confidence limit is below -12% we will conclude that DTG + FTC is potentially inferior to cART.

For the secondary comparison of the primary outcome between the two monitoring arms, we will calculate a Mantel-Haenszel test statistics and Mantel-Haenszel risk difference (DTG+FTC - cART) stratified for the type of treatment.

Secondary categorical outcomes (proportions of virological suppression <50 copies/mL both as a standard proportion and as FDA snapshot, of loss of future treatment options, of adverse events, of serious adverse events, of CSN adverse events, of CNS symptoms) between the DTG+FTC and cART groups, and between the patient-centered and standard monitoring groups will also be analysed using the Mantel-Haenszel test statistics and Mantel-Haenszel risk difference (DTG+FTC - cART) stratified for the type of monitoring and type of treatment, respectively.

For continuous outcome variables (CD4 count, HIV-DNA level, total cholesterol, high-density lipoproteine, triglycérides, low density lipoprotein-cholesterol, glucose, Framingham-calculated cardiovascular risk, glomerular function rate, weight, health-related quality of life, treatment satisfaction), we will compare the mean values at 48 months between the DTG+FTC and cART treatment groups and between the patient-centered and standard monitoring groups using linear regression adjusted for the type of monitoring and type of treatment, respectively.

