#### 11.4.3 Secondary analysis

For categorical outcomes, we will additionally calculate relative risk differences between groups. We will calculate odds ratios from multiple logistic regression models adjusting for the type of monitoring and type of treatment as appropriate. For repeatedly measured categorical outcome variables (virological suppression <50 copies/mL), we will consider a mixed effects logistic regression with a random intercept on the subject to account for within-patient correlations.

For repeatedly measured continuous outcome variables, we will also consider all measurements in a linear mixed effects regression model to account for within-patient correlations. Finally, we will analyse development over time by exploring the functional relationship between outcome and time using fractional polynomials and a treatment-by-time interaction term.

Moreover, we will evaluate all outcomes in crude analyses not adjusting for type of monitoring or type of treatment. Binary outcomes will be compared by the Chi-squared or Fisher's exact test, continuous outcomes by the Student t-test.

Cost-effectiveness of treatment arms (incremental cost-effectiveness ratio) will be calculated by taking the difference in mean costs between patient-centered arm and standard monitoring arm, and between DTG + FTC dual therapy arm and cART arm, and dividing them by the difference in time to loss of virological response (TLOVR) between the study arms. Difference in TLOVR will be assessed by comparing the area under the patient-centered and standard monitoring Kaplan-Meier curves, and under the DTG+FTC and cART Kaplan-Meier curves. Generalised lo-rank test will be used to compare times between groups.

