| RCT, 48W switch study in experienced pts ( DOMONO )                                                    | N = 104 pts on cART for 40 months with CD4 nadir of 340; randomized to immediate switch to DTG monotherapy or deferred switch after 24W                                                                                                                                                                    | Confidential (see e-mail by [name] 21.1.20): when 77/96 on DTG monoT pts had reached W48 of monotherapy, VF had developed in 8 (2 before W24, 6 after W24) . This led to the premature study discontinuation. Although DTG monoT was non-inferior to cART at W24, VF continued to occur after W24 and led to DTG resistance in 3 . Final results at CROI 2017                                                                                                                                                     |                                                                                                                              |
| RCT in experienced pts with VL <50 cp/mL on current ART ( DOLAM )                                      | N = 450; randomized 1:1:1 to DTG, DTG + 3TC, or current treatment (control). Follow-up at BL, 4, 12, 24, 36, 48W.

Pts on stable triT with <50 cp/mL in ≥2 consecutive determinations for ≥12 months, no prior VF or resistance mutations to 3TC/FTC or INSTI, nadir CD4 >200cells/mm  . | Confidential (see e-mail by [name] on 9.2.2017): 2 VF in monoT arm at the end of phase A (90 pts, 24W follow-up). According to DSMB advise (called according to protocol safety rules “DSMB will review the data if the proportion of confirmed virological failure in any of the experimental arms reaches ≥5%”), the Steering Committee has decided to interrupt the DTG arm and to continue the DOLAM study with two arms: CONTROL and DTG+3TC (no safety issues in dualtherapy arm). Results expected after October 2017 |                                                                                                                              |

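### Section 11.4.5 names ordinary logistic regression as the comparison for loss of future drug options. It has no finite odds ratio if an arm has no event, and it is not ranked against the Mantel-Haenszel analysis in 11.4.2.

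*Protocol*

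**What the plan says.** The outcome is defined in Protocol section 5.2: "Proportion of patients experiencing loss of future drug options defined as new intermediate or high-level resistance to one or more drugs" to which the virus was sensitive at entry. Section 9.2.2 restricts its assessment to patients failing treatment, meaning two consecutive HIV-RNA values of at least 100 copies/ml.

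Three sections describe its analysis:

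- **11.4.2** lists it among the secondary categorical outcomes ("of loss of future treatment options, of adverse events, of serious adverse events"), which "will also be analysed using the Mantel-Haenszel test statistics and Mantel-Haenszel risk difference". For the drug comparison the stratification is by monitoring type.
- **11.4.3** adds, as secondary analysis of categorical outcomes: "We will calculate odds ratios from multiple logistic regression models adjusting for the type of monitoring and type of treatment as appropriate". It also plans crude analyses: "Binary outcomes will be compared by the Chi-squared or Fisher's exact test".
- **11.4.5**, the safety analysis, repeats the definition and says the proportion "will be compared between the two treatment arms by a multiple logistic regression model adjusted for the monitoring strategy".

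On frequency, section 11.2 says: "The exceptions are rare outcomes such as adverse events, resistance or clinical complications for which the statistical power to detect differences will be low". No event rate for this outcome is given anywhere.

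**The concern.** One outcome has two main-sounding analyses with different effect measures: a risk difference in 11.4.2 and an odds ratio in 11.4.5. Nothing in 11.4.5 marks its model as secondary, so a reader cannot tell which result is the planned safety comparison.

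The model in 11.4.5 is also a poor fit for so rare an outcome. Ordinary maximum-likelihood logistic regression has no finite treatment odds ratio when all events fall in one arm, and no defined one when there are no events at all. Events on dual therapy with none on cART would be an unfavourable safety pattern, and this model could not put a size on it. Replacing the model after it failed to converge would be a deviation to be justified under 11.4.6, and the choice would be made with open-label data in view.

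**Working it through.** **Inputs**

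- Section 11.2: 92 patients per drug arm; assumed suppression of 97% on cART and 94% on DTG + FTC, so 3% and 6% not suppressed; margin 12%; one-sided level 0.025; power 80%.
- Supplementary file SF1: in the DTG monotherapy trial with 8 virological failures, "VF continued to occur after W24 and led to DTG resistance in 3".
- Section 3.1: no resistance to integrase inhibitors or the accompanying NRTIs in three cited first-line DTG combination trials.
- Assumed, because the protocol gives none: event rates of 0.5–6% on DTG + FTC and 0.5–3% on cART. The upper ends treat every non-suppressed patient as losing an option.

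**The plan's own figure.** With unpooled variance, n = (1.960 + 0.842)² × (0.97 × 0.03 + 0.94 × 0.06) / (0.12 − 0.03)² = 7.85 × 0.0855 / 0.0081 ≈ 82.9, hence 83 per group, as stated. Then 166 / 0.90 = 184.4, against the 184 stated.

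**Chance of an empty arm.** An arm of n patients with event rate p has no event with probability (1 − p)ⁿ. Writing a and b for the two arms, the chance that at least one is empty is a + b − ab.

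| DTG + FTC / cART rate (assumed) | n = 92 per arm | n = 83 per arm |
|---|---|---|
| 0.5% / 0.5% | 86% | 88% |
| 1% / 0.5% | 78% | 81% |
| 1% / 1% | 64% | 68% |
| 2% / 1% | 49% | 54% |
| 3% / 1% | 43% | 48% |
| 3% / 2% | 21% | 25% |
| 6% / 3% | 6% | 8.5% |

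For the last row at n = 92: 0.94⁹² = 0.003 and 0.97⁹² = 0.061, together 0.064.

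Borrowing the monotherapy ratio for both arms gives 0.06 × 3/8 = 2.25% and 0.03 × 3/8 = 1.125%, or about 2.1 and 1.0 expected events among 92. The chance of an empty arm is then 43% by the binomial formula and 44% by the Poisson one: 1 − (1 − e^−2.07)(1 − e^−1.04).

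**What each method gives with an empty arm.** Take 3 events in 92 on DTG + FTC (2 and 1 in the two monitoring strata of 46) and none in 92 on cART.

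- *Logistic model of 11.4.5.* After 5, 10, 20 and 30 Newton-Raphson steps the treatment coefficient is 2.8, 7.8, 17.8 and 27.8, with standard errors of 2.4, 28, about 4,160 and about 618,000. It does not converge.
- *Mantel-Haenszel risk difference.* Each stratum has weight 46 × 46 / 92 = 23. The estimate is (23 × 2/46 + 23 × 1/46) / 46 = 1.5 / 46 = 3.3 percentage points. The Greenland-Robins standard error is 1.85 points, so the 95% interval is −0.4 to +6.9. (This is not the interval of reference 107, whose formula the protocol does not give.)
- *Fisher's exact test, crude.* p = 0.25.
- *Firth logistic regression.* Odds ratio about 7.2, finite.

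If neither arm has an event, the Mantel-Haenszel difference is zero and so is its Greenland-Robins variance, so that interval says nothing either. At 92 per arm this has probability 40% at 0.5% / 0.5% and 4% under the borrowed ratio.

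**The case against.** The strongest reply is that the protocol already contains what is needed. Section 11.4.3 plans logistic odds ratios in addition to the Mantel-Haenszel analysis, so the two measures are meant to coexist, and it plans a crude Fisher's exact test. With events in one arm only, the trial would still have a finite stratified risk difference and a valid p-value. That stands: a reader might infer a flat contradiction, or that the resistance question would go unanswered, and the protocol supports neither. What it leaves open is the rank of the 11.4.5 model.

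A second reply is that sparse-data fallbacks belong in the SAP, which is not shown. That would hold if 11.4.5 were silent. It names a specific method instead, and that method fails under plausible data.

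A third concerns importance. A reader might take new resistance to be the main safety concern, but section 3.7 names virological failure as the main risk. The DSMB trigger in 11.3 is a count of patients, not an odds ratio, and 11.2 already concedes low power for resistance. This stands and limits the weight of the point.

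A fourth concerns the 43–44%. The 3-in-8 ratio comes from monotherapy, and nothing in the protocol supports carrying it to dual therapy or to cART. The 6% and 3% are non-suppression rates, which may overstate confirmed failures. The figure is therefore an illustration, and the range is the result. In the other direction, section 11.5 says its missing-value approach will be considered for secondary outcomes. If missing counted as a lost option, empty arms would be rarer, but the protocol does not say whether the rule applies to resistance.

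Finally, 11.4.5 does not specify Wald inference. A likelihood-ratio test and a one-sided profile bound would still exist, so it would go too far to say that every inference from the model fails. What fails is the odds ratio itself.

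**Conclusion.** The point holds as one of ranking and fitness of method. Section 11.4.5 gives ordinary logistic regression as the treatment comparison for an outcome that 11.4.2 already assigns to a more robust analysis, and does not say which leads. An arm with no event is realistic at 92 per arm: about 6% to 86% over the assumed rates, with the low end reached only if every non-suppressed patient loses an option. With events in one arm only, the odds ratio is infinite, while the risk difference of 11.4.2 and the exact test of 11.4.3 can still be reported.

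The size rests entirely on assumed event rates. The failure of the maximum-likelihood odds ratio does not; it follows from the method. The consequence is confined to a low-power secondary and safety outcome, and neither the primary non-inferiority conclusion nor the sample size changes.

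**What to change.** In 11.4.5, state that the main treatment comparison for loss of future drug options is the Mantel-Haenszel risk difference of 11.4.2, stratified by monitoring type, with the confidence interval method cited there (reference 107). That citation is attached to the primary comparison, so its use for this outcome should be written out. The protocol gives only the reference's title, so its behaviour with very few events should be confirmed.

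Add that any logistic odds ratio for this outcome, under 11.4.3 or 11.4.5, is supportive and is fitted by exact or penalised (Firth) logistic regression when an arm has no event. The logistic model need not be deleted; ranking it is enough. If neither arm has an event, report the counts.

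The cost is a sentence or two in 11.4.5. No new data, sample size change or change to the primary analysis is needed.

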#### **11.4.6 Deviation(s) from the original statistical plan**

A statistical analysis plan will be written before the end of the first year of participants enrolment. It will describe in details the statistical analyses answering the primary research question but also answering secondary research questions. It will detail how data will be described depending on their format. Once data will be available, the statistician in charge of the statistical analyses will apply the statistical analysis plan. Any deviations from the planned analyses will be at least described and justified.

### **11.5 Handling of missing data and drop-outs**

The following strategies will be used to replace missing values at the final study timepoint. If HIV-RNA is available at week 36, the value at time 36 will be considered (last observation carried forward). If no data is available at weeks 36 and 48, we will consider these patients as failures. The same approach will be considered for secondary outcomes. For continuous outcomes, we will exclude patients from the analysis if no data is available at weeks 36 and 48. In the snapshot analysis, patients with missing outcome in the time snapshot window will be considered as failures. Sensitivity analyses will be performed to determine whether the conclusions are sensitive to assumptions about the missing-data mechanism. We will compare patient characteristics between the two groups having or not missing data in order to assess their similarity. If differences are outlined, missing data would be considered not at random and some bias in the estimation of treatment effect would be suspected. If not, we will consider the complete case analysis as valid to estimate the noninferiority of DTG+FTC compared to standard treatment.

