### 3.4 Clinical Evidence to Date

#### ***Dolutegravir efficacy data in maintenance monotherapy***

DTG monotherapy as maintenance treatment in an ART experienced population was proved to be feasible, with a high rate of effectiveness over 24 weeks in three observational studies (49, 72, 73). *Katlama et al* enrolled 28 patients virologically controlled for 6.6 years with a median nadir CD4 count of 215 cells/mm^3. The proportion of patients with viral load <50 copies/ml at week 24 was 89% (25/28 patients). Three virological failures were reported: all occurred in patients previously exposed to first generation integrase inhibitors, and patients developed signature mutations for integrase inhibitors at week 24. Patients were however switched back to conventional triple ART regimen with virological success. The study by *Rojas et al* included 33 patients, virologically controlled for 8 years and with a mean nadir CD4 count of 229 cells/mm^3 (SD ±125); 97% of patients remained with an undetectable viral load at 24 weeks. One patient, previously failing on raltegravir, demonstrated virological failure with HIV-DNA genotypic resistance test showing a signature mutation for integrase inhibitor at week 24. *Oldenbuettel et al* enrolled 31 patients virologically suppressed for 24 weeks. One patient discontinued for adverse event (ongoing cough) and one presented with virological failure at week 24. This latest patient continued on DTG monotherapy for five more weeks; the genotypic resistance test at that time showed major INSTI mutations (73).

However, an academic-driven randomized controlled trial of DTG mono-maintenance therapy (the DOMONO trial - NCT02401828) in which 104 HIV virologically suppressed patients were enrolled to an immediate or delayed (at week 24) switch to DTG monotherapy and followed throughout 48 weeks from the date of switch, was prematurely stopped because of virological failure in 10% of patients (74, 75). While DTG monotherapy was non-inferior to cART at week 24, most of virological failures occurred after week 24 and led to INSTI-associated resistance mutations in three patients.

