### 3.7 Risks / Benefits

The main risk in this trial is virological failure on DTG + FTC dual therapy. In the ART Cohort Collaboration of 18 cohorts from Europe and North America including about 17900 patients, low level viremia measured between 50 and 199 copies/ml was weakly associated with virological failure (aHR 1.38, 95%CI 0.96-2.00) (85). We will measure HIV-1 RNA level in the plasma on a regular basis to monitor for low level viremia. Any patient with HIV-1 RNA  $\geq 100$  copies/ml will undergo an additional HIV-1 RNA measurement 14 days later ( $\pm 5$  days), as well as additional adherence session and review of concomitant medications and dolutegravir and emtricitabine plasma concentration measurements.

We will define virological failure as plasma HIV-1 RNA  $\geq 100$  copies/ml on two consecutive measurements. Any patient reaching virological failure will be assessed for genotypic resistance and pharmacogenetic analyses. This latest analysis will be only done in patients who are included in the SHCS and have also signed a consent form for genetic studies. In case of virological failure, the patient will undergo an additional medical visit with review of adherence, concomitant medications, discussion of results of DTG + FTC plasma concentration. Patients randomised in the DTG + FTC dual therapy arm will be switched to a standard cART regimen while waiting for results of genotypic resistance. Patients randomised in the continuing cART arm will await results of the genotypic results. In both cases, treatment will be adjusted according to genotypic resistance results. All failing patients will complete study procedures until week 48. Figure 3 presents the algorithm for the management of virological failure.

Any patient with HIV-RNA between 20 and 99 copies at any time of scheduled visits will have an additional HIV-RNA measurement after 6 weeks (+/-5 days).

Figure 3: Algorithm for the management of virological failure

[figure not shown]

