## 5. STUDY OUTCOMES

### 5.1 Primary Outcomes

The *first primary outcome* for the comparison between DTG + FTC dual therapy and standard cART is the proportion of patients maintaining HIV suppression defined as HIV-RNA <100 copies/ml throughout 48 weeks (+/- 21 days). A single blip defined as HIV-RNA <200 copies/ml during the study period is allowed as long as this value is followed by HIV-RNA <50 copies/ml.

The *second primary outcome* for the comparison between patient-centered and standard monitoring is the direct costs of the two study arms from the health care system perspective at week 48.

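### The ITT rule carries the week-36 HIV-RNA to week 48 whatever the reason for leaving, so neither required analysis counts late loss as failure to stay suppressed for 48 weeks

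*Protocol*

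**What the plan says.** Section 5.1 of the Protocol sets the first primary outcome as the proportion "defined as HIV-RNA <100 copies/ml throughout 48 weeks (+/- 21 days"). One blip under 200 copies/ml "is allowed as long as this value is followed by HIV-RNA <50 copies/ml".

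Section 11.5 gives the replacement rule for a missing final value: "If HIV-RNA is available at week 36, the value at time 36 will be considered (last observation carried forward"). It continues: "If no data is available at weeks 36 and 48, we will consider these patients as failures". For the secondary outcome at 50 copies/ml, the same section takes the stricter line: "In the snapshot analysis, patients with missing outcome in the time snapshot window will be considered as failures". It also announces sensitivity analyses on the missing-data mechanism without specifying them.

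Section 11.4.1 excludes from the per-protocol set anyone without a week-48 result (±21 days), unless virological failure came earlier. It requires the per-protocol and ITT analyses to reach the same conclusion before non-inferiority is claimed.

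Three other provisions bear on the point:
- The study schedule calls for a 2-week retest after a value of 100 or more. After 20-99 copies/ml, section 3.7 says the patient "will have an additional HIV-RNA measurement after 6 weeks (+/-5 days").
- Sections 8.5 and 9.2.5 ask patients who leave early to attend a close-out visit with the week-48 assessments.
- Section 7.4 keeps DTG + FTC patients who stop study drug in follow-up to week 48, provided that the new regimen still meets the eligibility criteria.

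**The concern.** The endpoint is a statement about 48 weeks, and the rule awards it to patients whose last 12 weeks were not observed. Take a patient with every value below 20 through week 36 who then leaves and provides no further sample. ITT scores this patient a success and per-protocol removes the patient. A patient whose last value was at week 24 is scored a failure.

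In a non-inferiority trial, crediting unobserved time favours the non-inferiority conclusion if late leavers are more common in the switched arm. The trial is open-label and only one arm changes drugs, so unequal leaving cannot be excluded. Requiring two analyses to agree is meant as protection, but here it gives none: one analysis credits the late leaver and the other omits the patient.

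The rule is also not what its label says. It names the week-36 value, not the latest one. Retests triggered at week 36 fall at about week 38 or 42, before the window opens at week 45. Section 11.5 does not say how these values, or a close-out value, enter the derivation.

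**Working it through.** **Inputs.** Section 11.2 gives success of 97% (cART) and 94% (DTG + FTC), margin 12 points, one-sided alpha 0.025, power 80%, 83 per arm raised to 92, and at least 10% loss. Section 5.1 gives a window of ±21 days, so it opens at week 45. The Protocol gives no timing of loss and no split by arm; both are assumed below.

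**1. The plan's own sample size.** n = (1.96 + 0.842)² × (0.97×0.03 + 0.94×0.06) / (0.12 - 0.03)² = 82.8, so 83 per arm. The stated figure is reproduced and is not in dispute.

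**2. Expected late leavers per arm.** Assume 10% loss spread evenly over 48 weeks. A value is missing but carried forward if the patient leaves between weeks 36 and 45:
- 92 × 0.10 × 9/48 = 1.7 patients (1.9 points).

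Counting to week 48 gives 92 × 0.10 × 12/48 = 2.3. This is too many, because leaving after week 45 need not mean a missing value.

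**3. Effect on the lower 95% limit.** Planned rates on 92 per arm are about 86 successes on DTG + FTC and 89 on cART. Unstratified Wald limit: d - 1.96 × √[p₁(1-p₁)/92 + p₂(1-p₂)/92]. The starting counts assume carry-forward; the later rows re-score late leavers as failures.

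| Late leavers re-scored (DTG + FTC / cART) | Successes | Difference | Lower limit |
|---|---|---|---|
| 0 / 0 (rule as written) | 86 / 89 | -3.3 | -9.5 |
| 1 / 0 | 85 / 89 | -4.3 | -10.9 |
| 2 / 0 | 84 / 89 | -5.4 | -12.2 |
| 2 / 2 | 84 / 87 | -3.3 | -10.7 |

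Two in one arm only is enough to cross -12. Two in each arm is not.

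**4. Power at 92 per arm.** Assume 10% loss in both arms, with carried-forward patients succeeding at their arm's planned rate. Power = Φ[(0.12 - (p_c - p_t))/SE - 1.96].
- Current rule, 9/48 of loss carried forward: rates 0.97 × 0.91875 = 89.1% and 0.94 × 0.91875 = 86.4%; power 48%.
- Current rule, 12/48 carried forward: rates 89.7% and 87.0%; power 50%.
- All missing counted as failure: rates 87.3% and 84.6%; power 44%.

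Most of the fall from the 84% obtained at n = 92 with no loss comes from earlier loss, which section 11.5 already counts as failure.

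**5. A miscount in the other direction.** A value of 150 at week 36 with a retest below 20 at week 38 is an allowed blip under section 5.1. If the week-48 sample is missing and 150 is entered there, the patient can read as having a second unsuppressed value. Such cases should be rare.

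**The case against.** The strongest reply is that the rule is narrow. It reaches back one visit only, and patients missing both week 36 and week 48 are failures. Patients who stop study drug normally stay in follow-up, and those who withdraw are asked for a close-out sample. To benefit from the rule, a patient must leave the study and also miss the close-out visit. Missing-as-failure is already planned in the snapshot outcome, and sensitivity analyses are promised. All of this stands and limits the number affected. It does not change how the ITT rule scores those who remain, and the snapshot is a secondary outcome at a different threshold.

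Three stronger readings are tempting, and the Protocol does not support them.
- A reader might infer that later retests are discarded. Section 11.5 replaces a missing value; it does not say that observed values are set aside. A retest of 100 or more may still be caught because the endpoint covers the whole period. The text leaves this unsettled.
- A reader might infer that weeks 36-48 are known to be the period of highest risk. Section 3.4 does report that "most of virological failures occurred after week 24", but in a DTG monotherapy trial and counted from week 24. The same section reports 97% suppression at week 40 in a DTG + 3TC switch study.
- A reader might infer that the rule biases the comparison by a known amount. With equal late loss the difference hardly moves, and no document figure supports loss in one arm only.

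The difference from the snapshot rule is not a contradiction, since the two are separate outcomes.

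**Conclusion.** The point holds in this limited form. In the ITT analysis, a patient suppressed through week 36 with no later value counts as suppressed for 48 weeks. Per-protocol excludes that patient, so neither required analysis treats late loss as failure. The text also leaves open how retest and close-out values are used.

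The size is about 1.7 patients per arm, assuming 10% evenly spread loss and a window that opens at week 45. Whether this matters depends on the split between arms: two against none would reverse the conclusion at the planned rates, and two against two would not. These are unstratified limits on assumed counts, not predictions. The change should be made, because the result can turn on two patients whose final status was never observed.

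**What to change.** In the ITT analysis of the first primary outcome, count a patient with no HIV-RNA in the week-48 window (±21 days) as not having maintained suppression, as the snapshot analysis already does. Keep carry-forward as a named sensitivity analysis, based on the last HIV-RNA actually measured, including the 2- and 6-week retests and the close-out value. State that observed retests count toward the endpoint, and that a carried-forward value is not a second viraemic event under the blip allowance.

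This changes wording only; no new data are needed. The price is about two more failures per arm and, at 10% evenly spread loss, power of roughly 48-50% falling to about 44% under the planned rates.
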